### Data and sample collection

The research data will be collected and managed using the Chinese Clinical Research Public Management platform (Res Man). Res Man is an electronic data collection and management system that records the management process for clinical trials, subject baseline data recorded during the trial, result data, and other related data based on the Internet, and transmits all to the central database for preservation and management. The experimental data may only be accessed and operated by the research team. The principal investigator will have access to real-time data but cannot make any changes to it.

All data collection staff will be trained on managing research questionnaires and evaluating body measurements, in accordance with the standard research programs to ensure the high quality and consistency of the questionnaire. The quality of life evaluation scale Short-Form Health Survey 36 (SF-36) [33], COOP/WONCA charts [34], and gastrointestinal symptom rating scale (GSRS) will be completed before entering the group, after the final treatment, 12 weeks after the final treatment, and 24 weeks after the final treatment. The respiratory and circulatory disease follow-up records will be acquired 12 weeks after treatment and 24 weeks after final treatment.

The pulmonary function data will be collected by respiratory specialists to ensure consistency, and examinations will be performed before entering the group, after the final treatment, 12 weeks after the final treatment, and 24 weeks after the final treatment.

Before the participants join the intervention and placebo group, they will be trained on how to collect and transport samples. Nasal secretions will be collected face-to-face by members of the research group. The participants will receive a cryopreservation box about − 20 °C before the fresh feces are collected. After the samples have been collected and stored in the storage box, the members of the research group will be informed immediately to transport the samples to the laboratory.

The procedure for subject nasal specimen collection will include wiping the surface of nasal mucosa with sampling paper and immediately placing it in an aseptic cryopreservation tube. After the samples of the left and right nasal cavity are collected, they will be combined into one sample. After samples are collected, they will be sealed in a self-sealing bag, placed on dry ice, transported to the laboratory within 2 h, and stored at − 80 °C.

The subject intestinal samples will be collected by using the fecal collection bowl (to avoid urine mixing). Subsequently, the samples will be dipped with sterile cotton swabs and transferred to an aseptic freezing tube, frozen in liquid nitrogen for more than 4 h, and then transferred to − 80 °C for preservation.

On the consent form, participants will be asked if they agree to use of their data should they choose to withdraw from the trial. Participants will also be asked for permission for the research team to share relevant data with people from the Universities taking part in the research or from regulatory authorities, where relevant. This trial does involve collecting biological specimens for storage. All samples will be destructed after use.

### Outcome measures

The assessment included flora analysis of nasal and intestinal secretions and questionnaires from researchers (all Chinese versions). Assessments will be started before allocation at screening (T0, baseline), 4 weeks after the final treatment (T1, primary endpoint), 12 weeks after the final treatment (T2, secondary endpoint), and 24 weeks after the final treatment (T3, final endpoint). The timeframe of data collection and assessments is shown in Table 1 (the SPIRIT figure).

**Table 1 Tab1:**
[figure not shown]
SPIRIT figure showing time points for enrollment, interventions and assessment

#### Primary outcome measure

The main primary outcomes in the current study will be nasal and gut microbiota diversity analyzed by the 16S ribosomal RNA (rRNA) gene, using Illumina Hiseq (Novogene Bioinformatics Technology Co., Ltd., Beijing, China). The differences in diversity in the PM2.5 high-exposure group and PM2.5 low-exposure group will be analyzed. We will also assess the changes between the treatment group and the placebo group after the intervention of probiotics in the same way.

#### Secondary outcome measures

Secondary outcome measures include the following:
The subject health will be assessed with a concise SF-36 questionnaire and a COOP/WONCA Chart will be generated. The subject quality of life will be summarized on eight aspects: physical function, role-physical, bodily pain, general health, vitality, social functioning, role-emotional, and mental health.The gastrointestinal subject function will be evaluated with the score from the GSRS.A pulmonary function test will be performed to evaluate the influence of PM2.5 on subject pulmonary function.The long-term efficacy of probiotics will be evaluated by recording a follow-up table of cardiovascular (angina pectoris, arrhythmia, myocarditis, coronary heart disease, and heart failure) and respiratory diseases (respiratory infection, asthma, bronchitis, COPD) end-point events.The participants’ weight, blood pressure, body temperature, pulse, past medical history, reproductive history, personal medical history, vaccination history, smoking history, and drinking history will also be registered to assess the basic health status of the patient.

### Adverse events’ reporting and safety monitoring

The Culturelle capsule used in this trial is a commercially available dietary supplement; therefore, the safety risk of the participants may be controlled, and the Chinese Ethics Committee of Registering Clinical Trials (Ethical Review No.: ChiECRCT20190173) has approved the study. We will ensure that every participant is aware of common adverse events related to the treatment in this study (such as indigestion or diarrhea), as well as serious adverse events (classified as life-threatening, permanently incapacitating, or requiring hospitalization) through the written consent form and detailed face-to-face consultations. During the treatment, participants must report any adverse events they may experience to the project team members, who must also record any adverse events they may have observed. All adverse events will be collected and presented promptly in detail to the project supervisor, who will determine the subsequent handling (including intimate observation, additional medical management, or early termination of participation) and record both the adverse events and the final outcomes in the CRF.

### Adherence to study interventions

We will use several strategies to encourage and monitor compliance with research interventions. Clear oral and written instructions will be provided during the 7-month period from the beginning of the screening, to the end of the follow-up. The content will include guidance on lifestyle assessment and adherence to daily research capsule intake. Two weeks after the beginning of the study, all participants will be contacted to assess how they manage interventions and, if necessary, further personalized guidance will be provided. All unused medicines will be returned and documented.

### Statistical methods

Analysis will be performed using BMISPSSStatistics24.0 software. Results will be considered statistically significant if *p* ≤ 0.05. Since the data should compare changes within groups, between groups and between-groups, and in order to reduce the probability of errors, two-way analysis of variance of repeated measurements will be used to explore the impact of time and time-group effects, and Bonferroni post-test will be used to adjust. Analysis of variance (ANOVA) and Bonferroni post-processing analysis were used for comparison between-groups. Covariance analysis will be used to adjust the effects of confounding variables. Baseline descriptive data between the intervention and placebo group will be compared using chi-square for categorical variables and *t* tests for continuous variables. The primary outcome of intestinal and nasal microbiota will be performed with the R Programming Language 3.0.1 (NZL).

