### Sample size

Sample size calculation was performed with G*Power 3.1 [30], using *F* test between factors with two groups (intervention and placebo) and three evaluation sessions (before administration, after administration, 12 and 24 weeks after administration). Since there was no pre-experiment before, we chose to take the average effect as 0.25, an *α* error probability of 0.05, and a power (1-β error probability) of 0.80. We take the Corr among rep measures as 0; the Nonsphericition correction ɛ is 1/(4–1) ≈ 1.34; the resulting total sample size is 95, because it has to be repeated 4 times; and the final sample size of each group is 24. Allowing for a maximum dropout rate of 30%, the number of subjects in the treatment group has been set to 30 participants. Based on the needs of our project, it is proposed to recruit high PM2.5 exposure and low PM2.5 exposure groups, and the groups are divided into intervention and placebo groups, according to each group requires a sample size of 30 patients, for a total of 120 patients.

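### T1 is named the primary endpoint, but the stated ANOVA is a four-level time-by-group test with pre-treatment T0 as a level; no baseline-adjusted T1 contrast is designated primary

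*Protocol article*

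**What the plan says.** **Endpoint.** Outcome measures (protocol article) calls T0 the baseline and attaches the primary endpoint to the next visit: "4 weeks after the final treatment (T1, primary endpoint". T2 is the secondary and T3 the final endpoint.

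**Test.** Statistical methods opens its reasoning with "Since the data should compare changes within groups, between groups and between-groups". It then names a two-way repeated-measures ANOVA for time and time-group effects with a Bonferroni post-test, and separately an ANOVA with Bonferroni for comparison between groups. No visit is named for either. For the microbiota primary outcome, the section gives only the software, R.

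**Levels of the ANOVA.** Sample size describes the calculation as "using *F* test between factors with two groups (intervention and placebo" and lists "three evaluation sessions (before administration, after administration, 12 and 24 weeks after administration". The count says three, but four visits are listed, the first before treatment, and the section later works with four repeats.

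**Covariates and baseline tests.** "Covariance analysis will be used to adjust the effects of confounding variables"; the variables are not named. "Baseline descriptive data between the intervention and placebo group will be compared using chi-square for categorical variables", and continuous variables by t tests.

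**The concern.** The endpoint and the stated test answer different questions. A time-by-group test over T0 to T3 is significant if the arms' profiles diverge at any visit. It can be driven by T2 or T3, and it spreads its power over three degrees of freedom. Treatment cannot have separated randomised arms at T0, so that visit contributes most as a covariate and least as an outcome level.

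Two smaller matters go with this:
- Significance tests of baseline variables between randomised arms test a null hypothesis that randomisation already makes true, so they tell the reader nothing useful.
- Within-group change is listed as a comparison. Enrolment runs from October to July, so such change mixes treatment with time and season. Only the contrast between arms is protected by randomisation.

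At stake is whether the trial yields one clear answer at its primary time point, and some power.

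**Working it through.** **1. The plan's own figure.** Inputs from Sample size: "an *α* error probability of 0.05, and a power (1-β error probability) of 0.80"; "we chose to take the average effect as 0.25" (Cohen's f, equal to d = 0.5 for two groups); m = 4 measures; correlation 0; stated total N = 95. The nonsphericity correction is given as 1/(4-1) but printed as 1.34; the arithmetic value is 0.333.

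- Within factor or time-by-group: λ = f²·N·m·ε/(1-ρ), with df (m-1)ε and (N-2)(m-1)ε. With ε = 0.34, λ = 0.0625 × 95 × 4 × 0.34 = 8.075, df = 1.02 and 94.86, power = 0.801. The smallest N reaching 0.80 is 95, as stated. With ε = 1/3 it is 97.
- Between factors, as the text names it: λ = f²·N·m/(1+(m-1)ρ). At N = 34, λ = 0.0625 × 34 × 4 = 8.5, df = 1 and 32, power = 0.807. This route gives N = 34, not 95.

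So 95 comes from a within or time-by-group F test with T0 as one of four levels.

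**2. Power of that test against a T1 contrast.** Assumptions, none fixed by the documents: SD 1, compound symmetry, sphericity, 0.5 SD at T1, two-sided 0.05, no dropout. The arms have 60 each with exposure strata pooled, or 30 each within one stratum (n = number per arm).

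- Time-by-group: λ = (n/2)·Σ(d_j - d̄)²/(1-ρ), with df 3 and 3(2n-2).
- Baseline-adjusted T1: noncentrality = d·√(n/2)/√(1-ρ²), with df 2n-3.

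Differences between arms at T0 to T3:
- Persistent (0, 0.5, 0.5, 0.5): d̄ = 0.375, sum of squares 0.1875.
- T1 only (0, 0.5, 0, 0): d̄ = 0.125, sum of squares also 0.1875, hence the same power.
- Decaying (0, 0.5, 0.25, 0.125): d̄ = 0.21875, sum of squares 0.1367.

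Example, n = 60 and ρ = 0.5:
- Persistent: λ = 30 × 0.1875/0.5 = 11.25, power 0.81.
- Decaying: λ = 30 × 0.1367/0.5 = 8.20, power 0.66.
- Adjusted T1: 0.5 × 5.477/0.866 = 3.162, df 117, power 0.88.

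| n per arm | ρ | Time-by-group, T1 only or persistent | Time-by-group, decaying | Adjusted T1 |
|---|---|---|---|---|
| 60 | 0 | 0.48 | 0.36 | 0.78 |
| 60 | 0.3 | 0.65 | 0.50 | 0.81 |
| 60 | 0.5 | 0.81 | 0.66 | 0.88 |
| 60 | 0.7 | 0.96 | 0.88 | 0.97 |
| 60 | 0.8 | 0.997 | 0.977 | 0.995 |
| 30 | 0 | 0.25 | 0.19 | 0.48 |
| 30 | 0.3 | 0.35 | 0.26 | 0.51 |
| 30 | 0.5 | 0.48 | 0.36 | 0.59 |
| 30 | 0.7 | 0.72 | 0.57 | 0.76 |
| 30 | 0.8 | 0.890 | 0.762 | 0.887 |

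A simulation of 4,000 trials (n = 30, persistent effect) agrees: 0.25 against 0.47 at ρ = 0, and 0.49 against 0.58 at ρ = 0.5.

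**3. The route to T1 that the plan does offer.** An unadjusted T1 comparison has power 0.78 at 60 per arm. As a post-test with Bonferroni over four visits (α = 0.0125), it has 0.58, and 0.27 at 30 per arm.

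**The case against.** **A T1 test exists.** A reader might infer that the plan has no test of T1. It plans Bonferroni post-tests and a between-group ANOVA, and either can include T1. What is lacking is the designation of one as primary.

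**Covariate choice.** A reader might infer that confounders are picked from the baseline p-values, or that the T0 value is ruled out as a covariate. The document states no selection rule: the two sentences are merely close together. The covariates are unnamed, so T0 is neither included nor excluded, and an article may leave that list to an analysis plan. This narrows the point but does not remove it, because the document does fix T0 as an outcome level.

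**Application to the microbiota outcome.** Statistical methods names only R for it. That the four-visit ANOVA applies there is an inference, supported by the way 95 reproduces.

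**The loss is conditional.** Against a T1-only or persistent effect, the two approaches are level near correlation 0.8. For a decaying effect the adjusted contrast stays ahead there, by a narrowing margin. At the plan's own correlation of 0, an unadjusted T1 test has the same 0.78, so the gain comes wholly from targeting T1.

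**The averaged group effect.** A much larger loss might be read into a group main effect averaged over four visits: its power is 0.17/0.14/0.12 at correlations 0.3/0.5/0.7 for an effect at T1 only. But Statistical methods names time and time-group effects, and 95 does not reproduce as a between-factors test. For a persistent effect the averaged test has 0.84/0.73/0.64, above the adjusted T1 contrast at 0.3. Those low figures should not be used.

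**Conclusion.** The point holds as a mismatch between endpoint and test, and should be corrected. The primary endpoint is at T1, the stated ANOVA does not target T1, and no T1 contrast or T0 covariate is designated.

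Under the assumptions above and correlations 0.3 to 0.7, power rises from between 0.65 and 0.96 to between 0.81 and 0.97 with 60 per arm (T1-only or persistent effect). With 30 per arm it rises from between 0.35 and 0.72 to between 0.51 and 0.76. The gain is larger if the effect decays. The only correlation in the documents is an assumed 0, so the size is a range and not an estimate.

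The lack of a designated T1 test does not depend on any of these assumptions. The baseline tests and within-group comparisons are secondary faults of wording. The document does not say that a within-group change would be reported as efficacy.

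**What to change.** - For each primary diversity index, define the primary test as the probiotic-placebo difference at T1. Obtain it from ANCOVA, or from a mixed model with T1 to T3 as outcome visits, with the T0 value as covariate and exposure stratum as a factor.
- Report the T2 and T3 contrasts from the same model as secondary.
- Name any further covariates in advance.
- Drop significance tests from the baseline table of the randomised arms.
- State that within-group changes are descriptive.
- Reconcile the timing of T1. Outcome measures puts it four weeks after final treatment; Data and sample collection puts the corresponding questionnaire and lung-function assessments after final treatment, with no interval. The primary contrast needs one agreed visit.

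The cost is analysis wording. T0 is already collected for the microbiota, lung-function and questionnaire outcomes. It is not collected for the cardiovascular and respiratory end-point events, which are recorded only 12 and 24 weeks after treatment, so baseline adjustment of this kind does not extend to them.

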## Discussion

Exposure to PM2.5 can significantly increase the risk of respiratory and circulatory diseases. Clinical epidemiological evidence has demonstrated that symptoms of chronic bronchitis and abnormal pulmonary function are closely related to exposure to PM2.5 [35, 36]. Both short-term and long-term exposure to PM2.5 can directly lead to an increase in the incidence of respiratory diseases, clinical consultation rates, and hospitalization rates [37–39]. The microorganisms carried by PM2.5 induce the pro-inflammatory response of resident immune cells, increase intestinal permeability, and change the lumen environment of the intestine, leading to growth of specific microbial strains better suited for survival in an inflammatory environment. These changes in the microenvironment will alter the intestinal microbiota of the host [40–42].

Since few studies currently exist for reducing the toxicological effects of PM2.5, any additional effective interventions would be very valuable. It is accepted that the microecosystem plays a significant role in health, and interventions to modify the microbiota are demonstrating value for treatment of several conditions related to individual health. Probiotics form the basis of the interventions in this study and have the potential to address specific health concerns. The purpose of this study is to evaluate the protective effect of probiotics in subjects with high exposure to PM2.5 and to investigate possible microbial molecular mechanisms. The study results should provide valuable information regarding health maintenance and pharmaceutical intervention of probiotics in individuals with high exposure to PM2.5.

## Trial registration

The trial was pre-registered at the China Clinical Trials Registry on 27 August 2019 under the registration number ChiCTR1900025469. See http://www.chictr.org.cn/index.aspx

## Trial status

This paper is based on protocol version 2.0 dated 25 September 2019. Recruitment began in October 2019, and approximate date of completion is July 2020. Any major protocol changes will be notified to the ethics committee and updated on the Chinese Clinical Trial Registry.

## Modification of the protocol

Any changes to the protocol may affect the process of the study, which will be agreed between the project leader and the supervisor, inform the sponsors and all members of the research group, and also need to be approved by the Ethics Committee; any deviations of the protocol will be fully documented using a breach report form.

## Data Availability

Data sharing is not applicable to this article as no datasets are reported. Availability of datasets generated in the study will be included in papers reporting study outcomes. Access to the full protocol and model consent forms may be available from the author upon reasonable request.

## Abbreviations

CRF: Case report forms
DSMB: Data and safety monitoring board
FAO: Food and Agriculture Organization
GSRS: Gastrointestinal symptom rating scale
LGG: *Lactobacillus rhamnosus* GG
PM2.5: Fine particulate matter that have a diameter of less than 2.5 μm
Res Man: Research Public Management platform
SF-36: Short-Form Health Survey 36
SPIRIT: Standard Protocol Items: Recommendations for Interventional Trials
TCM: Traditional Chinese Medicine
WHO: World Health Organization
